## Appendix 5: Performance Status Evaluation

### ECOG PERFORMANCE STATUS

| Grade | ECOG                                                                                                                                                      |
|-------|-----------------------------------------------------------------------------------------------------------------------------------------------------------|
| 0     | Fully active, able to carry on all pre-disease performance without restriction                                                                            |
| 1     | Restricted in physically strenuous activity but ambulatory and able to carry out work of a light or sedentary nature, e.g., light house work, office work |
| 2     | Ambulatory and capable of all selfcare but unable to carry out any work activities. Up and about more than 50% of waking hours                            |
| 3     | Capable of only limited selfcare, confined to bed or chair more than 50% of waking hours                                                                  |
| 4     | Completely disabled. Cannot carry on any selfcare. Totally confined to bed or chair                                                                       |
| 5     | Dead                                                                                                                                                      |

### KARNOFSKY PERFORMANCE STATUS SCALE DEFINITIONS RATING (%) CRITERIA

|                                                                                                                     |     |                                                                                     |
|---------------------------------------------------------------------------------------------------------------------|-----|-------------------------------------------------------------------------------------|
| Able to carry on normal activity and to work; no special care needed.                                               | 100 | Normal no complaints; no evidence of disease.                                       |
|                                                                                                                     | 90  | Able to carry on normal activity; minor signs or symptoms of disease.               |
|                                                                                                                     | 80  | Normal activity with effort; some signs or symptoms of disease.                     |
| Unable to work; able to live at home and care for most personal needs; varying amount of assistance needed.         | 70  | Cares for self; unable to carry on normal activity or to do active work.            |
|                                                                                                                     | 60  | Requires occasional assistance, but is able to care for most of his personal needs. |
|                                                                                                                     | 50  | Requires considerable assistance and frequent medical care.                         |
| Unable to care for self; requires equivalent of institutional or hospital care; disease may be progressing rapidly. | 40  | Disabled; requires special care and assistance.                                     |
|                                                                                                                     | 30  | Severely disabled; hospital admission is indicated although death not imminent.     |
|                                                                                                                     | 20  | Very sick; hospital admission necessary; active supportive treatment necessary.     |
|                                                                                                                     | 10  | Moribund; fatal processes progressing rapidly.                                      |
|                                                                                                                     | 0   | Dead                                                                                |

## Appendix 6: Quality of Life Assessments

### EORTC QLQ-C30 (version 3)

We are interested in some things about you and your health. Please answer all of the questions yourself by circling the number that best applies to you. There are no "right" or "wrong" answers. The information that you provide will remain strictly confidential.

Please fill in your initials: **bbbb** Your birthdate (Day, Month, Year): **ddmmyyyy**

Today's date (Day, Month, Year): **ddmmyyyy**

#### Not at All (1), A little (2) Quite a Bit (3) Very Much (4)

- 1 Do you have any trouble doing strenuous activities, like carrying a heavy shopping bag or a suitcase? 1 2 3 4
- 2 Do you have any trouble taking a long walk? 1 2 3 4
- 3 Do you have any trouble taking a short walk outside of the house? 1 2 3 4
- 4 Do you need to stay in bed or a chair during the day? 1 2 3 4
- 5 Do you need help with eating, dressing, washing yourself or using the toilet? 1 2 3 4

#### During the past week: Not at All (1), A little (2) Quite a Bit (3) Very Much (4)

6. Were you limited in doing either your work or other daily activities? 1 2 3 4
7. Were you limited in pursuing your hobbies or other leisure time activities? 1 2 3 4
8. Were you short of breath? 1 2 3 4
9. Have you had pain? 1 2 3 4
10. Did you need to rest? 1 2 3 4
11. Have you had trouble sleeping? 1 2 3 4
12. Have you felt weak? 1 2 3 4
13. Have you lacked appetite? 1 2 3 4
14. Have you felt nauseated? 1 2 3 4
15. Have you vomited? 1 2 3 4
16. Have you been constipated? 1 2 3 4

Please go on to the next page

[figure not shown]

**During the past week: Not at All (1), A little (2) Quite a Bit (3) Very Much (4)**

17. Have you had diarrhoea? 1 2 3 4
18. Were you tired? 1 2 3 4
19. Did pain interfere with your daily activities? 1 2 3 4
20. Have you had difficulty in concentrating on things, like reading a newspaper or watching television? 1 2 3 4
21. Did you feel tense? 1 2 3 4
22. Did you worry? 1 2 3 4
23. Did you feel irritable? 1 2 3 4
24. Did you feel depressed? 1 2 3 4
25. Have you had difficulty remembering things? 1 2 3 4
26. Has your physical condition or medical treatment interfered with your family life? 1 2 3 4
27. Has your physical condition or medical treatment interfered with your social activities? 1 2 3 4
28. Has your physical condition or medical treatment caused you financial difficulties? 1 2 3 4

**For the following questions please circle the number between 1 and 7 that best applies to you**

29. How would you rate your overall health during the past week? 1 2 3 4 5 6 7 (Very poor-Excellent)
30. How would you rate your overall quality of life during the past week? 1 2 3 4 5 6 (Very poor-Excellent)

© Copyright 1995 EORTC Quality of Life Group. All rights reserved. Version 3.0

## EORTC QLQ -BN20

Patients sometimes report that they have the following symptoms. Please indicate the extent to which you have experienced these symptoms or problems during the past week.

**During the past week: Not at All (1), A little (2) Quite a Bit (3) Very Much (4)**

- 31. Did you feel uncertain about the future? 1 2 3 4
- 32. Did you feel you had setbacks in your condition? 1 2 3 4
- 33. Were you concerned about disruption of family life? 1 2 3 4
- 34. Did you have headaches? 1 2 3 4
- 35. Did your outlook on the future worsen? 1 2 3 4
- 36. Did you have double vision? 1 2 3 4
- 37. Was your vision blurred? 1 2 3 4
- 38. Did you have difficulty reading because of your vision? 1 2 3 4
- 39. Did you have seizures? 1 2 3 4
- 40. Did you have weakness on one side of your body? 1 2 3 4
- 41. Did you have trouble finding the right words to express yourself? 1 2 3 4
- 42. Did you have difficulty speaking? 1 2 3 4
- 43. Did you have trouble communicating your thoughts? 1 2 3 4
- 44. Did you feel drowsy during the daytime? 1 2 3 4
- 45. Did you have trouble with your coordination? 1 2 3 4
- 46. Did hair loss bother you? 1 2 3 4
- 47. Did itching of your skin bother you? 1 2 3 4
- 48. Did you have weakness of both legs? 1 2 3 4
- 49. Did you feel unsteady on your feet? 1 2 3 4
- 50. Did you have trouble controlling your bladder? 1 2 3 4

© Copyright 1994 EORTC Study Group on Quality of Life. (phase III module)

---

## Appendix 7: QTc with Bazetts Correction

$$QTcB \text{ (mSec)} = \frac{QT \text{ (mSec)} \times 0.04}{\sqrt{RR \text{ (mSec)} \times 0.04}}$$

**QTc:** QT Interval (time between the start of the Q wave and the end of the T wave on the ECG trace)

**RR:** interval from the onset of one QRS complex to the onset of the next QRS complex, often derived from the heart rate (HR) as 60/HR

Mean QTcB to be calculated, e.g from a prolonged rhythm strip.

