### 5.1.2 Exclusion Criteria

Any of the following is regarded as a criterion for exclusion from the study:

- Patients on enzyme-inducing anti-epileptic drugs (see [section 7.5](#)) within 2 weeks prior to study enrolment. Note: Patients are eligible if they switched to non-enzyme inducing agents and discontinued enzyme-inducing agents for more than or equal to 2 weeks prior to randomisation
- Inadequate bone marrow reserve as demonstrated by an absolute neutrophil count  $\leq 1.5 \times 10^9$  /L or platelet count  $\leq 100 \times 10^9$  /L or requiring regular blood transfusions to maintain haemoglobin  $>9\text{g/dL}$
- Serum bilirubin  $\geq 1.5 \times \text{ULRR}$  (except for patients with known documented cases of Gilbert's Syndrome)
- ALT or AST  $\geq 5 \times \text{ULRR}$
- Serum creatinine  $>1.5 \times \text{ULRR}$  or a creatinine clearance of  $\leq 50\text{mL/min}$  calculated by Cockcroft-Gault

- Greater than +1 proteinuria on two consecutive dipsticks taken no less than 1 week apart unless urinary protein <1.5g in a 24 hr period or UPC (Urine Protein: Creatinine) ratio <1.5
- History of significant gastrointestinal impairment, as judged by the investigator, that would significantly affect the absorption of cediranib or gefitinib, including the ability to swallow the tablet whole
- Patients with a history of poorly controlled hypertension with resting blood pressure >150/100mmHg in the presence or absence of a stable regimen of anti-hypertensive therapy, or patients who are requiring maximal doses of calcium channel blockers to stabilise blood pressure
- Any evidence of severe or uncontrolled diseases (e.g. unstable or uncompensated respiratory, cardiac, hepatic or renal disease)
- Unresolved toxicity >CTC AE grade 1 from previous anti-cancer therapy (including radiotherapy) except alopecia (if applicable)
- Mean QTc with Bazetts correction >470msec in screening ECG or history of familial, long QT syndrome (see Appendix 7)
- Cardiac ventricular arrhythmias requiring anti-arrhythmic therapy
- Significant haemorrhage (>30mL bleeding/episode in previous 3 months) or haemoptysis (>5mL fresh blood in previous 4 weeks)
- Recent (<14 days) major surgery or brain biopsy. Recent craniotomy (<28 days) prior to first dose, or a surgical incision that is not fully healed
- Pregnant or breast-feeding women or women of childbearing potential with a positive pregnancy test prior to receiving study medication (see [section 5.1.3](#))

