## 5.2 Pre-randomisation evaluation

Patients must give written informed consent before any trial specific screening investigations may be carried out. The following assessments or procedures are required to evaluate the suitability of patients prior to entry:

- Confirmation (histological/cytological) that patient has glioblastoma (WHO grade IV)
- Within 7 days prior to randomisation:
  - Brain Tumour assessment: MRI scan of the tumour region, where the tumour is the largest. –See [section 7.7](#) (Imaging) for the list of required scans.
  - Demographic details including date of birth, sex, and race
  - Relevant medical and surgical history, including previous hypertension, ongoing medication and documentation of baseline symptoms
  - Physical examination: height and weight, vital signs (including pulse, lying and 5 min standing blood pressure, respiratory rate and temperature)
  - ECOG performance status
  - Karnofsky performance status

- Mini-mental status exam
- Neurological examination
- Full blood count (FBC)
- Serum biochemistry: sodium, potassium, urea, creatinine, phosphate, total protein, albumin, globulin, adjusted calcium, total bilirubin, alkaline phosphatase, AST and/or ALT, LDH and gamma-GT.
- Clotting function tests (PT/APTT)
- Thyroid function tests
- Urinalysis: dip-stick test for protein. If a patient has two consecutive urine protein measurements of greater than one plus (+) taken no less than 1 week apart then measure urine protein:creatinine ratio or collect a 24-hour urine for total protein. A urine protein/creatinine ratio of 0.15 (urine protein and urine creatinine expressed in mg/dl) approximates a 24-hour urine protein of 150mg/24 hours or 0.15 g/24 hours, which is the upper limit of normal.
- Pregnancy test (if applicable – i.e females of child bearing potential (see [section 5.1.3](#)))
- ECG with estimation of QTc interval (see Appendix 7)

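### The Appendix 7 formula is not Bazett's correction in the units it states, and a QTcB calculated by hand with it as printed cannot exceed the 470 msec screening exclusion

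*Protocol*

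**What the plan says.** Section 5.1.2 of the protocol lists as an exclusion: "Mean QTc with Bazetts correction >470msec in screening ECG or history of familial, long QT syndrome". It refers the reader to Appendix 7. Section 5.2, on pre-randomisation evaluation, requires "ECG with estimation of QTc interval (see Appendix 7", so the screening ECG is tied to the same appendix. Section 8.2 note b adds that ECGs are to be evaluated in the week before randomisation to confirm eligibility, and section 5.1 allows no exceptions to eligibility.

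Appendix 7 prints the formula. The numerator is QT, labelled mSec, times 0.04. The denominator is the square root of RR, labelled mSec, times 0.04. The result is labelled mSec. The legend then says that RR is "often derived from the heart rate (HR) as 60/HR" and closes with "Mean QTcB to be calculated, e.g from a prolonged rhythm strip". The protocol gives no other QTc formula and no worked example.

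**The concern.** Bazett's correction divides QT by the square root of RR expressed in seconds, and the result takes the unit of QT. The printed version departs from this in two ways.

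- A factor of 0.04 is applied to quantities labelled in milliseconds. It looks like the conversion from small ECG squares (0.04 s each) to seconds. The appendix never mentions squares, so that origin is my inference.
- RR is labelled in milliseconds in the formula but derived as 60/HR, which is in seconds: at a heart rate of 60 it equals 1, not 1000.

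The formula serves an eligibility rule with a numerical limit. If its output is not on the scale of the limit, a site that follows the appendix literally would pass every patient on that limb, including patients whose true QTcB is above 470 msec.

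**Working it through.** **Inputs from the protocol.** Threshold: mean QTcB above 470 msec (section 5.1.2). Formula: QT × 0.04 / √(RR × 0.04), all labels mSec, with RR derived as 60/HR (Appendix 7). The protocol states no calculated QTc value, so there is no figure of its own to reproduce.

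**Assumed inputs.** The protocol gives no example ECG. I take QT 400 ms at heart rate 60 (RR 1000 ms = 1 s = 25 small squares; QT = 10 small squares) as a normal ECG, and QT 360–600 ms with heart rate 50–120 as a range.

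**Reference.** Bazett: QT (ms) / √(RR in s). For the normal ECG, 400 / √1 = 400 ms.

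**Three readings of the printed formula, normal ECG:**

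- (a) Both inputs in ms, as labelled: 400 × 0.04 / √(1000 × 0.04) = 16 / 6.325 = 2.53.
- (b) QT in ms, RR = 60/HR in seconds: 16 / √(1 × 0.04) = 16 / 0.2 = 80.
- (c) Both inputs in small squares: 10 × 0.04 / √(25 × 0.04) = 0.4 / 1 = 0.40. This is the right Bazett value in seconds, under a label that says mSec.

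**Ratio to Bazett in ms.** Under (a) it is 0.04 / √(0.04 × 1000) = 0.00632, or 0.63%. Under (b) it is 0.04 / √0.04 = 0.2, or 20%. Both ratios are the same for every QT and heart rate, so they do not depend on the example chosen.

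**Further examples:**

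| QT, heart rate | Bazett (ms) | (a) RR in ms | (b) RR in s | (c) squares |
|---|---|---|---|---|
| 400 ms, 60 | 400 | 2.53 | 80 | 0.40 |
| 480 ms, 60 | 480 | 3.04 | 96 | 0.48 |
| 440 ms, 75 | 492 | 3.11 | 98 | 0.49 |
| 600 ms, 120 | 849 | 5.37 | 170 | 0.85 |

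The last three rows exceed 470 msec by Bazett, and none does under any reading of the printed formula. Over the whole assumed range, (a) gives 2.1 to 5.4 and (b) gives 66 to 170.

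**What 470 would require at heart rate 60.** Under (a), QT = 470 × √40 / 0.04 ≈ 74,300 ms. Under (b), QT = 470 × 0.2 / 0.04 = 2,350 ms, more than twice the 1000 ms RR interval. Even with QT stretched to fill the whole RR interval, the printed result is 6.3 under (a) and 200 under (b). Under (c) the output is in seconds, so 470 would mean a QTc of 470 seconds.

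**The case against.** The strongest reply is that the error gives itself away. A QTcB of 2.5 or 80 msec beside a limit of 470 msec is plainly implausible. Section 5.1.2 names Bazett's method as well as pointing to the appendix, and many sites may read QTcB from the ECG machine. Sections 6.1 and 12.3 provide a central eligibility check before randomisation, and section 12.3 also provides range checks on stored data. This stands as mitigation. It makes a silent failure less likely, but it does not make the formula right. The protocol does not say whether QTc is calculated or machine-read, nor that the QTc value is recorded on a form where a range check would see it.

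A reader might infer that the trial has no cardiac screen at all. The documents do not support that: the familial long-QT limb and the separate exclusion for ventricular arrhythmias needing treatment do not use Appendix 7. A reader might also infer that QTc in the safety reporting is spoiled. Sections 2.6.3 and 16.5 list only ECG parameters, without naming QTc or Appendix 7, and the ECG row of the assessment schedule in section 8.1 does not cite it either. I make no claim about the on-study ECG summaries.

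Finally, the formula reached me by program from a PDF, so a misread label is possible. The factor 0.04 appears in both numerator and denominator, which makes a reading error unlikely. The printed page should settle it.

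**Conclusion.** The point holds for screening eligibility. As printed, Appendix 7 is not Bazett's correction in its stated units. Its output is 0.63% of Bazett with RR in milliseconds, 20% with RR in seconds, or the correct value in seconds under a millisecond label if squares are entered. In each case no physiologically plausible ECG exceeds 470, so literal hand use would disable the numeric limb of that exclusion.

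The consequence is conditional on a site calculating by hand with the formula as it stands; how often that would happen cannot be told from the protocol. The example ECGs are assumptions, but the two ratios are not. No endpoint, sample size or planned analysis is affected. It still deserves correction before use, because this is the only QTc method in the protocol and it governs who may be randomised.

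**What to change.** Replace the Appendix 7 formula with QTcB (ms) = QT (ms) / √(RR in seconds), with RR = 60/HR, and state the unit of each term. Label the legend entry that defines the uncorrected interval as QT; it is now headed QTc. Add one worked example, for instance QT 440 ms at heart rate 75: RR = 60/75 = 0.8 s, and 440 / √0.8 = 492 ms. If counting small squares is to be offered, give it as a separate line with inputs labelled as numbers of squares and the result converted from seconds to milliseconds.

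The cost is one re-issued appendix page. If any patients have already been screened, check each QTcB that was calculated by hand. The threshold in section 5.1.2 needs no change for this purpose.

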## Appendix 8: MRI Acquisition form

Circle Visit:

Patient Trial Number: **DRC**.....

Patient Initials:.....

Date of Scan: .....

Hospital: .....

|          |          |          |          |          |         |                 |         |
|----------|----------|----------|----------|----------|---------|-----------------|---------|
| Baseline | Week 6   | Week 12  | Week 18  | Week 24  | Week 30 | Week 36         | Week 42 |
| Week 48  | Week 54  | Week 60  | Week 66  | Week 72  | Week 78 | Week 84         | Week 90 |
| Week 96  | Week 102 | Week 108 | Week 114 | Week 120 | Other:  | Discontinuation |         |

| IMAGE                                                                       |                     | Orientation | Pulse parameters           |                      |                           | Flip Angle | Matrix | FOV | Slice gap (mm) | Slice thickness (mm) | No of acquisitions |
|-----------------------------------------------------------------------------|---------------------|-------------|----------------------------|----------------------|---------------------------|------------|--------|-----|----------------|----------------------|--------------------|
|                                                                             |                     |             | TR (Repetition Time) /msec | TE (Echo time) /msec | TI (Inversion time) /msec |            |        |     |                |                      |                    |
| FLAIR (Fluid-attenuated inversion-recovery image)                           | Required Parameters | Axial       |                            |                      |                           |            |        |     | 0mm            | 3                    |                    |
|                                                                             | Actual parameters   |             |                            |                      |                           |            |        |     |                |                      |                    |
| DWI (diffusion weighted image)
Spin echo –echo planar                    | Required Parameters | Axial       |                            |                      |                           |            |        |     | 0mm            | 3                    |                    |
|                                                                             | Actual parameters   |             |                            |                      |                           |            |        |     |                |                      |                    |
| T2 (T2-weighted fast spin echo images)                                      | Required Parameters | Axial       |                            |                      |                           |            |        |     | 0mm            | 3                    |                    |
|                                                                             | Actual parameters   |             |                            |                      |                           |            |        |     |                |                      |                    |
| T1 volumetric (three-dimensional gradient echo images)                      | Required Parameters | Coronal     |                            |                      |                           |            |        |     | 0mm            | 1                    |                    |
|                                                                             | Actual parameters   |             |                            |                      |                           |            |        |     |                |                      |                    |
| Post-contrast T1 volumetric (three-dimensional gradient echo images) | Required Parameters | Coronal     |                            |                      |                           |            |        |     | 0mm            | 1                    |                    |
|                                                                             | Actual parameters   |             |                            |                      |                           |            |        |     |                |                      |                    |
| Post-contrast FLAIR (Fluid-attenuated inversion-recovery image)      | Required Parameters | Axial       |                            |                      |                           |            |        |     | 0mm            | 3                    |                    |
|                                                                             | Actual parameters   |             |                            |                      |                           |            |        |     |                |                      |                    |

Staff member completing form:.....

Please return this form with a copy of the scans on CD in DICOM format to the DORIC Trial Coordinator, CR-UK & UCL Cancer Trials Centre, [name].

---

